**STUDY PROCEDURES**

Before the trial, all the children will be evaluated carefully, and the research topic will be explained to the parents of the Children with ASD who meet the study’s selection criteria. If they are then willing to participate in the trial, they will receive the supplements free of charge for three months and carry out the relevant inspections and tests. They will sign an informed consent agreement. They will be able to consult with the doctors if they have any questions when they are administering the supplements, but they must follow the requirements of the agreement. If they are not willing to continue the study for some reason, they can withdraw. All the potential side effects will be monitored and all the participants will be recalled at 3 months after intervention for the systematic physical examination and liver as well as kidney function analysis. The potential costs will be covered by indemnity for negligent harm. The participants will be asked to provide a one tube faeces sample 0, 1, 2, and 3 months after taking the supplements, and a tube of blood with heparin anticoagulation at 0 and 3 months. To guarantee quality all samples must be transported within 12 hours at low temperatures or they will be rejected. Other than the samples used for flow cytometry detection, which has to be completed within 12 hours, all samples will be aliquots and frozen in a freezer at -80℃.

**Consent**

This study has been approved by the Ethics Committee of the Third Affiliated Hospital of Zhengzhou University (2020-56). Randomisation will be done after the researcher explain the details of the clinical study to the guardian of the children and sign the informed consent. Consent written must be documented by a witness.

**Diagnosis and treatment**

**Diagnosis**

It meets the diagnostic criteria of ASD established in the American Diagnostic Statistical Manual of Psychiatry 5th edition^[17]^: (1) persisting deficits in social communication and social interaction in different environments;(2) limited and repetitive interests, behaviors, or activities;(3) These symptoms exist in early development; (4) These symptoms cause significant impairments in professional, social, or other vital functions; (5) Mental retardation or global developmental retardation cannot better explain these symptoms;

Meeting the above criterion can be diagnosed as ASD, of which (1)(2) is the core symptom of ASD. The child was diagnosed with autism spectrum disorder need by three senior specialists in the same field.

**Assessment of** **core symptoms**

All parents/guardians will be asked to complete an Autism Treatment Evaluation Checklist (ATEC) ^[32]^ to evaluate changes in core symptoms in Children with ASD at the time of the baseline, the third month, and the sixth month respectively. The scale consists of four subscales: speech, perception, social interaction, and behaviour. The total score is 0-179; the higher the score, the more serious the condition. The reduction rate of ATEC score before (S1) and after (S2) treatment will be used as the efficacy index (N), N = (S1- S2)/S1 × 100%. Markedly effective: NM ≥ 50%, Effective: NE: 20%−50%, Ineffective: NI < 20%. Total effective rate (NT) = (NM + NE) / total cases × 100%.

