**STATISTICAL ANALYSIS**

**Randomisation and masking**

Randomisation was stratified according to severity, gender, age (3−6 years or 7−12 years). Participants will be allocated (1:1) to the probiotics or placebo group using a concealed random allocation from a computer-generated random numbers table produced by Python (a cross-platform computer programming language). The additives used for the placebo group will have the same packaging, taste, and weight as the experimental group, except for the ingredients. All participants and doctors will be blind to the allocation of treatments.

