**Sample size calculation**

The sample size will be calculated using Epitools (<https://epitools.ausvet.com.au/onemean>). The expected difference between the probiotic and placebo groups is based on a previous study on ASD, in which the standard deviation value of behaviour score was 8.32 in the ASD group^[31]^. To detect a clinically significant difference in the outcome measures with the condition of 90% power (α = 0.05; two-sided), 67 children are required for each group. Based on clinical study experience ^[40]^, we presume a drop-out rate of 19% through infection, efficacy, compliance, use of antibiotics, or other unforeseeable factors, implying a minimum of 80 children for each group.

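### Efficacy is defined as percent ATEC reduction cut at 20% and 50% and pooled into an effective rate; testing that rate loses information that a baseline-adjusted analysis of the score would keep

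*Protocol*

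**What the plan says.** Under *Assessment of core symptoms*, the protocol has parents or guardians complete the ATEC at baseline, month 3 and month 6. On the scale, "The total score is 0-179; the higher the score, the more serious the condition". Three steps then fix the efficacy measure:

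- Index: "The reduction rate of ATEC score before (S1) and after (S2) treatment will be used as the efficacy index (N"), with N = (S1 − S2)/S1 × 100%.
- Classes: "Markedly effective: NM ≥ 50%, Effective: NE: 20%−50%, Ineffective: NI < 20"%.
- Summary: "Total effective rate (NT) = (NM + NE) / total cases × 100"%, that is, the share of children whose score falls by at least 20%.

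*Primary Outcome Measure* lists efficacy evaluation first and disease severity second, and defines neither there. The ATEC index is the only definition of efficacy in the protocol.

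*Sample size calculation* works from a continuous quantity: "the standard deviation value of behaviour score was 8.32 in the ASD group". The target is "To detect a clinically significant difference in the outcome measures", with no numerical difference stated, and the result is "90% power (α = 0.05; two-sided), 67 children are required for each group". No expected response rate appears anywhere.

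*Randomisation and masking* adds: "Randomisation was stratified according to severity, gender, age" (3–6 or 7–12 years).

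**The concern.** Two features of the endpoint cost the trial something.

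First, dividing by the baseline score makes the fall needed to count as effective proportional to where the child starts. Entry requires a DSM-5 diagnosis and sets no minimum ATEC score, on a scale that runs to 179, so baselines can vary widely. A given improvement in points can then be a success in one child and a failure in another, and a response rate is hard to read as an amount of change in core symptoms.

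Second, pooling to at least 20% versus less than 20% treats a 21% fall and a 70% fall alike, and treats a 19% fall as no change. If that rate is what is tested, a real effect is more likely to be missed than the planned 90% power suggests, because the sample size was derived for a score and not for a rate.

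**Working it through.** **The plan's own figure.** The 67 per group cannot be recomputed forward, because no difference is stated. Solved backwards with SD 8.32 and multiplier 1.960 + 1.282 = 3.242:

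- two means: 3.242 × 8.32 × √(2/67) = 4.66 points;
- one mean (the cited calculator's address ends in onemean): 3.242 × 8.32/√67 = 3.29 points.

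Only the standardised effect is needed below. With two groups of 67, the effect detected with 90% power is 3.242 × √(2/67) = 0.560 SD. This does not depend on 8.32.

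**Dependence on baseline.** The fall needed for class effective is 0.20 × S1 and for markedly effective 0.50 × S1:

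| Baseline S1 | 20% | 50% |
|---|---|---|
| 20 | 4 points | 10 points |
| 60 | 12 points | 30 points |
| 120 | 24 points | 60 points |

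**Information lost by the single cut.** For a normally distributed outcome cut so that a share p responds, the fraction of information kept is φ(z)²/[p(1 − p)], with z the normal quantile at 1 − p. At p = 0.5: 0.3989²/0.25 = 0.637. At p = 0.3: 0.3477²/0.21 = 0.576. The documents give no p, so the whole range is shown:

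| Response rate | Information lost |
|---|---|
| 50% | 36% |
| 40% or 60% | 38% |
| 30% or 70% | 42% |
| 20% or 80% | 51% |
| 10% or 90% | 66% |

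**All three classes, analysed as ordered.** The corresponding sum over three classes gives losses of 19% (70% at or above the lower cut, 30% at or above the upper), 25% (50%, 10%) and 38% (30%, 5%). When response is rare (20%, 2%) the loss reaches 49%.

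**Power at 67 per group.** Shift a normal outcome by 0.560 SD and compare the shares beyond the cut with a two-sided 5% test of two proportions:

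| Control rate (assumed) | Treated rate | Power | n per group for 90% |
|---|---|---|---|
| 20% | 38.9% | 67% | 120 |
| 30% | 51.4% | 72% | 109 |
| 50% | 71.2% | 72% | 110 |
| 70% | 86.1% | 62% | 137 |

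**Cross-check by simulation.** This used 67 per group and 3,000 trials in each of six scenarios. The assumptions were a baseline ATEC mean of 50 or 70, SD 20 or 25, baseline–follow-up correlation 0.5 to 0.9, and a control fall of 0 to 20%. The effect was set for about 90% power by ANCOVA.

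- ANCOVA of the score: 89–90% power.
- Pooled 20% rate: 64–72%.
- Three ordered classes: 65–78%.

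**What baseline adjustment adds.** Relative to the unadjusted follow-up score, ANCOVA multiplies the variance by 1 − r²: 0.75 at r = 0.5 and 0.36 at r = 0.8. The documents give no r; these values are assumed.

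**The case against.** The protocol names no test for the ATEC, and a statistical analysis plan that is not shown may do so. The quoted index is itself a continuous percentage, so information is lost only if the classes or the pooled rate are what is compared. The use of a score SD in the sample size could even mean that a comparison of means was intended. These points stand as limits. They do not remove the finding, because the classes and the pooled rate are fixed in the protocol, and any test of the rate as defined inherits the loss.

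Four stronger readings are tempting, and the documents do not support them.

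- *A flat loss of about 40%.* That figure fits the single cut at response rates of roughly 30–70%. It is larger outside that range and usually smaller if three ordered classes are used. The documents give no response rate.
- *Bias from baseline dependence.* Allocation is randomised and stratified by severity, so the dependence acts alike on both arms in expectation. It affects precision and interpretation, not the validity of the comparison.
- *Many responders from noise alone.* With no true change and an assumed error SD of 6 for the difference, a child at baseline 20 has a 25% chance of being classed effective (4/6 = 0.67 SD). But under an assumed baseline mean of 65 and SD 22, a score of 20 is about 2 SD below the mean. At 65 the chance is about 1.5% (13/6 = 2.17 SD), and at 43 about 7.6% (8.6/6 = 1.43 SD).
- *Baseline and stratification factors are left unused.* The protocol is silent on covariates, which are commonly set in the analysis plan. Silence on this is not a fault.

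**Conclusion.** The concern holds in a limited form. The protocol itself fixes a categorised ratio as the measure of efficacy, and this is the only content given to the first primary outcome. The link to that outcome is an inference, but no other definition is offered. The endpoint is valid under randomisation but inefficient. It also classes equal point changes differently by baseline, which follows from the formula without any assumption.

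The power loss does rest on assumptions: a normally distributed outcome, the pooled rate as the tested quantity, and response rates the documents do not give. Over control response rates of 20–70%, an effect with 90% power on the score has about 62–72% power on the rate. Restoring 90% would take about 109 to 137 children per group instead of 67. Using the three classes as ordered reduces the loss but does not remove it. The change should be made, though the trial's validity does not depend on it.

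**What to change.** Amend *Assessment of core symptoms* and *Primary Outcome Measure* together:

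- Define the primary efficacy analysis as the between-group difference in ATEC total at one named visit already scheduled for the ATEC. Months 3 and 6 appear both there and under *Follow-up*.
- Estimate it by ANCOVA, or by a mixed model over visits, adjusted for baseline ATEC, severity, gender and age group, and report it with a 95% confidence interval.
- Keep the 20% and 50% classes and the total effective rate as descriptive secondary results.

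This also brings the analysis into line with a sample size set for a score. The cost is wording in two sections, the decision on which visit is primary, and a headline result in points rather than as a response rate. Baseline and follow-up ATEC, severity, gender and age are already collected, so no extra patients, visits or data are needed.

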**Assessment of severity**

CARS will be used ^[33]^. The scale consists of 15 items with a total score of 60 points. A score of less than 30 points means no autism is present, and a score of 30-60 points means autism is present; 30-37 points signifies moderate autism, and 37-60 points with at least five items and a score more than three points signifies severe autism.

**Assessment of sleep**

The Children’s Sleep Habits Questionnaire (CSHQ) is based on the International Classification of Sleep Disorders^[34]^. Each item uses a 3-level score based on the frequency of sleep-related behaviours, from low to high from 1 to 3 points, respectively. There is a total of 52 items; the higher the number, the greater the children’s sleep disorders. The questionnaire comprises eight common sleep disorders in children, namely: 1) sleep impedance; 2) delay in falling asleep; 3) sleep duration; 4) sleep anxiety; 5) waking at night; 6) parasomnia; 7) sleep breathing disorders; and 8) daytime sleepiness. The questionnaire uses the total score > 41 points as the standard for evaluating sleep disorders, and defines the standard for sleep disorders as a frequency of more than two nights a week in each item^[35]^.

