**Hypotheses**

Primary: Probiotic supplements could relieve the core symptoms of autism，such as the narrow range of interests or activities and repetitive and stereotypical behavior.

Secondary(a): Probiotics can help balance gastrointestinal disorders in children with autism, such as constipation and diarrhea.

Secondary(b): Metabolites from the gut flora help improve sleep disorders.

Secondary(c): The metabolites of intestinal flora contribute to the improvement of immunity.

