**Follow-up**

**1,2,3, 6,12months:** Assessment of Gastrointestinal tract, sleep, speech and communication skills, social skills, perceptual skills, health and physical behavior according to scale. (blinded assessment by certified study personnel)

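### The CSHQ cut-off of more than 41 lies below the lowest total that 52 items scored 1 to 3 can give, so as written it cannot separate children with and without a sleep disorder

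*Protocol*

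**What the plan says.** The protocol section Assessment of sleep makes four statements about the CSHQ.

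- Item scoring: "Each item uses a 3-level score based on the frequency of sleep-related behaviours, from low to high from 1 to 3 points, respectively".
- Length and direction: "There is a total of 52 items; the higher the number, the greater the children’s sleep disorders".
- Cut-off: "The questionnaire uses the total score > 41 points as the standard for evaluating sleep disorders".
- A second standard, in the same sentence as the cut-off: it "defines the standard for sleep disorders as a frequency of more than two nights a week in each item".

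The section lists eight sleep domains. It does not say that only some items are summed, and it gives no other scoring, such as one starting at zero. No other section changes the item count, the scoring or the cut-off.

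Sleep is the subject of secondary hypothesis (b), "Metabolites from the gut flora help improve sleep disorders", and is listed under Secondary outcome measures. Follow-up has it assessed with the other domains at 1, 2, 3, 6 and 12 months. Sample and data collection has the CSHQ results recorded with other candidate data and allows this information to be used for subgroup analysis.

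**The concern.** A cut-off is useful only if some children can fall on each side of it. Here the item count and the item scores together fix the lowest possible total, and the cut-off is below it. The item count, the scoring and the cut-off therefore cannot all describe the same total score.

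At stake is any use of the trial's own definition of a sleep disorder: the proportion affected in each arm, the number of children moving into or out of the category, or a subgroup of children with sleep disorder. If the contradiction is first noticed at analysis, someone must then decide which items to sum. A choice made after the data are seen would leave the sleep result open to selection.

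**Working it through.** **Inputs**, all from Assessment of sleep:

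- number of items: k = 52
- lowest item score: 1
- highest item score: 3
- sleep disorder if the total is above 41

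**Range of the total as described**

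- Minimum = k × 1 = 52 × 1 = 52
- Maximum = k × 3 = 52 × 3 = 156
- Gap between minimum and cut-off = 52 − 41 = 11 points

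A child with the best possible answer on every item scores 52, which is above 41. Every completed total therefore meets the definition. The proportion classed as sleep-disordered is 100% in each arm at each visit, and the difference between arms in that proportion is 0 whatever the true effect on sleep.

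**When could a cut-off of more than 41 discriminate?** With items scored 1 to 3, two conditions must hold:

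- a child can be at or below the cut-off: k × 1 ≤ 41, so k ≤ 41
- a child can be above the cut-off: k × 3 > 41, so k ≥ 14 (13 × 3 = 39 is not above 41; 14 × 3 = 42 is)

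The cut-off can therefore work only if between 14 and 41 items are summed. Exactly 41 items is still possible, because the minimum of 41 is not above the cut-off. The protocol names no such subset, so the intended number cannot be derived from it.

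**The per-item standard.** This rests on how many nights a week a behaviour occurs, not on a total, so the calculation above does not touch it. The text does not settle whether it labels single items as problems, must hold in every item, or is an alternative to or an addition to the total-score rule.

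**The case against.** The best defence has three parts.

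1. *The item count may describe the length of the questionnaire and not the scored total.* The section cites sources for the instrument and the cut-off, and a shorter scored set may be defined there. Those sources are not at hand, so this cannot be checked. If a standard scoring key is used, the data would be unaffected and the fault would be one of description. This stands as a possible explanation. It does not remove the defect, because the protocol does set out the scoring, and the only set of items it mentions is all 52.

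2. *No endpoint uses the cut-off.* This stands. The outcome list says only that sleep is measured, and Follow-up has it assessed according to the scale. The ATEC has a responder formula; the CSHQ has none. The cut-off is not an eligibility criterion, a stratification factor or an input to the sample size. A reader might infer that the trial could never show a sleep benefit. The documents do not support that: the protocol gives the score a graded meaning, with higher values worse, and a comparison of the continuous score remains open once the scored items are fixed.

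3. *The size is easy to overstate.* A reader might put it as all 160 children (2 × 80) at all visits. Sample size calculation presumes 19% drop-out, so the supportable statement covers children with a completed score. A reader might also treat this as a fault in the primary outcome, because the Synopsis includes sleep disorders in its primary outcome sentence. The same Synopsis places sleep disturbances among the secondary objectives, and Hypotheses and Secondary outcome measures both make sleep secondary. That conflict over the role of sleep is a separate matter and does not make this point more serious.

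**Conclusion.** The contradiction holds and is exact: the stated cut-off lies 11 points below the lowest total that the stated items and scores can produce. It rests on one assumption, that the total compared with 41 is the sum of all 52 items. That is how the text reads, and nothing in the protocol points to another sum.

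The consequence is limited to classification by the total score. A sleep-disorder rate, a change of category or a subgroup defined by more than 41 would be uninformative. It does not follow that every child is sleep-disordered under every definition in the section, because the per-item standard is a separate rule whose link to the total is left open.

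This should be fixed. It is a wrong decision threshold for a named secondary outcome, and not merely a detail left to a statistical analysis plan.

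**What to change.** Before the CSHQ data are analysed:

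1. Check item count, scored items and cut-off against the version of the instrument used, and state which items enter the total to which the cut-off applies. If items score 1 to 3 and the cut-off stays at more than 41, the number summed must lie between 14 and 41. The exact number has to come from the instrument.
2. Keep the full item count only as the length of the questionnaire, if that is what it is.
3. State how the per-item frequency standard relates to the total-score rule: whether it replaces it, adds to it or only describes single items.

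Optionally, compare the continuous CSHQ total on the stated items between arms, adjusted for the baseline score. This avoids dependence on a cut-off, but it is an analysis choice that the statistical analysis plan may already make and is not needed to resolve the contradiction.

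The cost is a few sentences in Assessment of sleep. No new data, visits or participants are needed.

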**Assessment of gastrointestinal symptoms**

Gastrointestinal symptoms will be assessed by gastrointestinal assessment questionnaires（GSRS）^[36]^ and the Bristol Stool Chart^[37]^.

**Major Rehabilitation Training**

Rehabilitation training includes applied behavioral analysis therapy (ABA) ^[38]^and structured education (TEACCH) ^[39]^.

**Sample and data collection**

Peripheral Blood: A vacuum vasculture containing heparin anticoagulant was used to collect 1-2mL of peripheral venous blood at the time of baseline, three months after probiotics administration, and the deadline.

Stool samples: Fecal samples were collected at the baseline, three months after probiotics administration, and the deadline, respectively. Temporary storage in -20℃ refrigerator within 1 hour, transported in ice bags within 24 hours, -80℃ storage .

The information of candidate's gender, age, history of asphyxia, family history, history of allergies, diet and the mother's history of pregnancy, hypertension during pregnancy, mode of delivery need to collect. At the same time, the diagnostic results of DSM-5 and the evaluation results of ATEC, CARS, CSHQ, GSRS and so on also need to be recorded. These information can be used for subgroup analysis.

**Follow-up**

**1,2,3, 6,12months:** Assessment of Gastrointestinal tract, sleep, speech and communication skills, social skills, perceptual skills, health and physical behavior according to scale. (blinded assessment by certified study personnel)

**Primary Outcome Measure**

- 1. Efficacy evaluation
  2. Severity of disease

**Secondary outcome measures**

1. Gastrointestinal symptoms
2. Sleep
3. Parental pressure
4. Eating habits
5. Diet pattarns
6. Metabolites in Blood and fecal
7. Immune cells
8. Abundance of intestinal flora

